Description of the tools used and variables retained:School performanceIndicators of school performance are obtained 2 years after the beginning of the intervention, based on national evaluations taking place in the first and second years of primary school in France (*EVALAIDE* in Grade 1 and Grade 2). These evaluations target various literacy and math skills: reading out loud words, reading out loud text, understanding phrases while reading them, writing syllables, writing words, operating phonemes, recognizing letters, comparing letters, knowing letters’ names and sounds, understanding words, understanding phrases, understanding texts, reading numbers, writing numbers, visualizing numbers, comparing numbers, ordering numbers in sequence, resolving math problems, calculating mentally, adding numbers, subtracting numbers, and reproducing geometrical forms. *Mathematic skills, Reading skills*: based on these tests, we will create two outcomes corresponding to mathematics and reading skills.Standardized observations*Individualized Classroom Assessment Scoring System (InCLASS):* The InCLASS is a standardized naturalistic observation tool analyzing 3 to 5 years old children’s interactions in a classroom context [34]. It comprises 10 dimensions: (1) positive engagement with the teacher (which comprises the following indicators: attunement to the teacher, proximity seeking, and shared positive affect with teacher), (2) communication with the teacher (conversation initiated and maintained with the teacher, and variety of speech with the teacher), (3) teacher conflict (aggression, negative affect, attention-seeking behaviors, and non-compliance toward the teacher), (4) peer sociability (proximity seeking, shared positive affect, cooperation toward peers, and popularity), (5) peer communication (conversation initiated and maintained with peers, and variety of speech with peers), (6) peer assertiveness (positive initiation of interactions with peers and leadership toward peers), (7) peer conflict (aggression, negative affect, attention-seeking and confrontation toward peers), (8) engagement with tasks (sustained attention and active engagement in classroom activities), (9) self-reliance (personal initiative and independence in classroom activities), and (10) behavior control (patience, activity level matching expectations, and physical awareness) [13]. These dimensions have been grouped into four domains in a previous study using confirmatory factor analyses [13]: positive engagement with teachers (grouping positive engagement and communication with teacher), positive engagement with peers (peer sociability, peer communication, and peer assertiveness), positive engagement with tasks (engagement with tasks and self-reliance), and negative classroom engagement (teacher conflict, peer conflict, and the reversed score of behavior control). This tool has demonstrated solid inter-rater reliability, construct validity, and criterion validity [34]. *Positive engagement with teachers score, Positive engagement with peers score, Positive engagement with tasks score, Negative classroom engagement score:* Each dimension is rated on a 7-point scale, with higher score indicating higher frequency and/or quality of behavior within a dimension. Data from each of the observation cycles—collected by each data collector—are averaged to obtain final dimension scores. Mean score for the four domains are then calculated by averaging final dimensions scores within each of the four domains. Inter-rater agreement is calculated based on 12.5% of all observations, where the two data collectors independently observe the same child.Tasks*Challenging Situations task (CST):* An app-version of the full CST task is used to assess children’s emotional response in challenging interpersonal problems and ability to solve interpersonal problems [28]). Situation, emotion vignettes, and behavioral response vignettes are displayed on a tablet and responses are automatically registered. Emotional responses are composed of four different choices: happy, indifferent (“just ok”), sad, and angry. Behavioral responses are composed of four types of choices: a prosocial choice, an aggressive choice, an avoidant choice, and a dysregulated (“crying”) choice [27]. Examiners describe each situation picture and ask what the child would do in such a situation, by presenting response picture choices and asking the child to point at the picture corresponding to their emotion/behavior when/if the situation happens. Previous studies suggested that choosing sad emotion and prosocial behaviors on the CST constitutes adaptive behaviors that are linked with emotion knowledge and peer acceptance [28], and predicts classroom adjustment, pre-academic literacy skills, kindergarten readiness and academic achievement [26, 27, 81]. On the opposite, choosing aggressive response is associated with poor peer acceptance [28], poor classroom adjustment, and poor academic readiness [27]. *Adaptive responses score, Aggressive behavior score:* Along with previous studies [26, 81], the proportion of adaptive responses (Sad emotion + Prosocial behavior” responses) and aggressive behavior responses across the six vignettes (ranging from 0 to 6) are calculated.*Emotion matching task-expressive knowledge:* The expressive knowledge sub-task of the Emotional Matching Task (EMT) measures 3 to 6- years-old children expressive emotion knowledge – i.e., the ability to recognize and label expressions of others’ emotions (based on Izard test [46, 55];). A sample of 12 colored photographs representing ethnically-diverse children with emotional facial expression are presented on a tablet screen: happiness, sadness, fear/surprise, anger, and mixed (anger/sadness). Children are asked each time what the child on the picture is feeling [55]. The EMT has demonstrated good criterion validity, strong reliability and construct validity [55], and preliminary evidence for cross-cultural validity has been found [3]. *Expressive emotional knowledge score:* Each child verbal responses are assigned to a score of 0 (= incorrect response), 1 (=accepted response), or 2 (=correct response). Accepted verbal responses are pre-determined and listed in a table before test sessions using the instruction manual. All items are summed to obtain the total score, with higher score indicating better expressive emotion knowledge.*Executive functioning battery:* We use an app-version of the EF battery (“*EF Touch*”), a battery of six EF tasks designed for preschool children from 3 to 5 years, which was found to show good criterion validity [83]. Each response is automatically registered on a computer communicating with the tablet. Analyses of dimensionality show that performance on EF tasks is best characterized by a single EF factor [83]. The Houses, Pick the Picture and Something the Same tasks, when combined, best approximate an EF latent variable underlying performance on all the six tasks [84]. We therefore selected these three tasks to assess children’s EF within a single EF latent factor model. Finally, following the suggestion of Willoughby et al. [84], only two randomly selected tasks out of three are administered to each child using a planned missing design, in order not to overload attention capacities of children and to reduce global test burden. Score for the missing parameter is estimated through an imputation procedure.*Houses game (also named Working Memory Span game):* This task assesses working memory span. Children are presented with houses in which are located a line-drawing animal and a color dot. They are asked to name both the animals and the colors in each of the houses. Then, animals and color dots disappear from houses. Children have to recall either which animal *or* which color was in the target house, thus holding in mind two pieces of information and activating one of them (i.e., animal name) while overcoming interferences from the other (i.e., color name) [84]. Task becomes increasingly difficult as the number of houses on the screen increases (from one to three houses).*Pick the Picture (PTP) game:* This is a self-ordered pointing task assessing working memory. In this task, children are asked to touch once each picture appearing on the screen, so that all of the pictures “get a turn” [84]. Between each touch, location of pictures is changed in a randomized order. Difficulty of the task increases as the number of pictures increases (from two to six pictures).*Something’s the Same (STS) game:* This task evaluates cognitive flexibility. For each item, children are asked to shift their attention from one dimension of similarity to another dimension of similarity [84]. Initially, they are presented with two pictures that share one dimension of similarity (e.g., color, shape, size, etc.). Then, a third picture is presented, and children have to tell how this new picture is similar to one of the original pictures. This last picture always shares a different dimension of similarity with one of the original pictures. In the second part of the game, all pictures are presented at once and children have to identify two different dimensions of similarity.*Working memory span score 1 (Houses), Working memory span score 2 (Pick the picture), Cognitive Flexibility Score*: for each EF battery game, each response is coded into a dichotomous variable (0 = incorrect response, 1 = correct response). The total score is a proportion ranging from 0 to 1, with 0 indicating no items correct and 1 indicating all items are correct.*Peer acceptance task:* The peer acceptance task measures how a particular child is accepted and liked by his peers in his/her class. It is a peer rating measure inspired by Asher et al. (1979) sociometric procedure [14]. Children are presented with photos of their classmates. After identifying classmates on these photos, they are asked to sort each photo of classmates into three envelopes: happy smiley for “I really like to play with this child”; neutral smiley for “I kind of like to play with this child”; unhappy smiley for “I don’t like to play with this child”. Answers are coded 3, 2, and 1 respectively. This procedure shows adequate reliability and validity [14]. *Peer acceptance score*: After testing each child, we assess how many times a child photo is put in each envelope: a mean score is calculated by summing up the score on each trial and dividing by the number of children in the classroom minus one. The final score indicates how much a child is accepted by his peers, with higher scores indicating higher levels of acceptance.*Sharing task:* This task evaluates child sharing. The sharing task used in this study is a sub-section of the task designed by Flook et al. [38], divided into two trials. For each trial, children are presented with 10 stickers. They are told that they can keep as many stickers as they want for themselves and share as many as they want with another child. They then separate stickers between two different envelopes (identified with the photo of the assessed child and the photo of the other child). In the first trial, the other child is the one identified by the assessed child as his/her most-liked classmate, and in the second trial, the other child is the one identified as the least-liked classmate. Sharing ability has been shown to differ between groups that received an SEL intervention compared to control group [38]. *Sharing proneness score*: 20 minus the total number of stickers (ranging from 0 to 20) put in the “me” envelope across the two trials is calculated. Higher scores indicate higher levels of sharing tendencies.Teacher-rated questionnaires*Commitment to implement:* Teachers in the intervention group are asked about their commitment to implement the program using a single item: “I feel motivated to use the program/strategies in my classroom”. Previous study indicates that this item is a valid indicator of teacher commitment to implement various evidence-based programs, regarding construct validity and convergent validity with other measures of commitment and with commitment predictors [22]. Teachers in the intervention group are also asked whether they liked the training, whether they found it useful, whether they found the content of the program useful, whether they liked the content of the program, and whether their students liked the content of the program. These items are rated on a 5-point Likert scale (from 1= “strongly disagree” to 5 = “strongly agree”). *Commitment score*: We will construct a standardized commitment score based on these previous items. Higher score indicates higher commitment to implement. As the psychometric properties of this score have not been validated, we will check the internal validity of the constructed score using Cronbach’s Alpha.*Preschool and kindergarten behavior scale (PKBS)- Social skills:* The PKBS social skills [54] is a teacher-rated scale assessing preschool and kindergarten children’s social skills. The French version of the scale is divided into 5 subscales [20]: The first subscale, “social interaction’ consists of 10 items that reflect behaviors and attitudes necessary to develop and maintain good relationships and friendship with others (such as defend others’ rights, helping others), “participates in classroom or family discussions,” “shows affection for other children,” or “tries to understand another child’s behavior.” The second subscale consists of six items and reflects components of “agreeableness with peers,” such as “plays with several different children,” “makes friend easily,” or “smiles and laughs with other children.” The third subscale, “compliance,” relates to respect for adult authority and social norms, such as “follows instructions from adults,” “follows rules,” or “uses free time in an acceptable way.” The fourth subscale, “cooperation with peers,” describes behaviors such as “shares toys and other belongings” or “gives in or compromises with peers when appropriate.” Finally, the fifth factor, labeled “autonomy,” is composed of items such as “works or plays independently,” “adapts well to different environments,” or “attempts new tasks before asking for help.” *Total PKBS Social Skills Score, PKBS Social interaction score, PKBS Agreeableness with peers score, PKBS Compliance score, PKBS Cooperation with peers scores, PKBS Autonomy score; PKBS functional level categorical score*: The 34 items are rated on a 4-point Likert scale ranging from 0 (= Never) to 3 (= Often). Total raw scores and raw scores for each subscale are calculated by adding scores of each item, with higher scores indicating better social skills. For 5–6-year-old children, total raw scores are divided into 4 functional level categories based on child age: “high functioning” (scores 95 to 102), “average” (scores 76 to 94), “moderate deficit” (scores 59 to 75), and “significant deficit” (scores 0 to 58) to compute a functional level categorical variable.*Strengths and difficulties questionnaire (SDQ)-extended teacher version*: The SDQ-extended teacher version is a scale used to measure children’s externalized symptoms, internalized symptoms, and pro-social behaviors [42]. It is divided into five factors of five items each: emotional symptoms, conduct problems, hyperactivity-inattention, peer problems, and prosocial behavior. At the end of the questionnaire, 4 items explore impacts of difficulties (overall distress, social impairment, learning impairment, and burden for teacher and classroom) [41]. The SDQ displays satisfactory reliability and validity [42] and although its factor structure in French language remains uncertain [15, 16], the SDQ French version shows satisfactory reliability and content validity for the total difficulties score [16]. *SDQ total difficulties score, SDQ impact score*: The 25 items are statements rated on a 3-point Likert scale indicating to what extent each statement applies to a target child, with 0 = Not true, 1 = Somewhat true, 2 = Certainly true. All factors except Prosocial behavior are summed in a Total difficulties score. Items relative to impact of difficulties are coded from 0 to 2, with 0 corresponding to no impact or little impact, 1 corresponding to “Somewhat impactful”, and 2 to “Very impactful”. An impact total score ranging from 0 to 8 is then generated by summing these items. Higher scores indicate higher levels of difficulties and higher level of impact.*Student-teacher relationship scale-short form (STRS):* The STRS-short form is a teacher-rated scale exploring teachers’ perspective on their relationship with a designed child in their classroom [60]. The scale comprises two distinct factors, one measuring the degree to which teacher-child relationship is characterized by warmth, positive emotions and open communication (closeness), and the other measuring the degree to which the relationship is characterized by negative emotions and interactions (conflict). This scale possesses excellent psychometric properties across multiple samples [60]. The validation of the French version is ongoing [21]. *STRS Closeness score, STRS Conflict score:* The 15 items (8 items assessing Closeness, 7 items assessing Conflict) are scored using a 5-point Likert scale ranging from 1 (= Definitely does not apply) to 5 (= definitely applies). Total scores are then calculated for each factor.Teacher personal well-being P-WB:*Comprehensive inventory of mindfulness experience (CHIME):* The Comprehensive Inventory of Mindfulness Experience (CHIME) is a self-report multidimensional scale measuring “dispositional” (or “trait”) mindfulness in adults with or without knowledge or previous contact with mindfulness [9, 53]. It captures the following eight dimensions of “trait” mindfulness: awareness of internal experience, awareness of external experience, acting aware, self-acceptance and non-judgment, non-reactivity, openness and non-avoidance, ability to relativize, and insight. The CHIME exhibited good reliability and satisfactory construct validity [9]. The validated French version of the scale used in this study showed highly satisfactory psychometric properties as well [71]. *CHIME Total score:* The 37 items are rated on a 6-point Likert scale (from 1 = “fully applies” to 6 “does not apply at all”). Total score is calculated by inverting each item score and adding all inverted score. Higher scores indicate higher proneness to experience mindfulness in everyday life.*Warwick-Edinburgh mental well-being scale (WEMWBS):* The Warwick-Edinburgh mental well-being scale (WEMWBS) is self-report single-factor measure composed of positively worded items related to positive mental health and well-being [74]. It covers a wide-range of concepts associated with positive mental health, including hedonic and eudemonic well-being, satisfying personal relationship, and positive functioning. The original version displayed good content validity and reliability [74], and the French version used in this study showed good internal consistency, stability and construct validity [77]. *WEMWBS Total score*: The 14 items are rated on a 5-point Likert scale (from 1= “never” to 5 = “always”), with high score indicating higher mental well-being.*Satisfaction with professional life scale (Echelle de Satisfaction de Vie Professionnelle; ESVP):* The ESVP scale is a unidimensional French short self-report measure of general professional life satisfaction derived from the Satisfaction with Life scale from Diener et al. (1985) [29, 39]. It displays adequate level of internal consistency and temporal stability, and good construct validity [39]. *ESVP total score*: The 5 items are rated on a 7-point Likert scale (from 1= “strongly disagree” to 7 = “strongly agree”), with higher scores indicating higher professional life satisfaction.

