#### Strategies to improve adherence to interventions {11c}

No specific strategy is implemented to improve adherence. However, to control and improve fidelity to intervention, implementation notebooks are distributed to teachers in the intervention group at the beginning of the program. Each week, teachers are asked to write down the curriculum activities that have been implemented each day, the duration of activities and to add comments if necessary. In the middle of the school year, teachers are also asked to record themselves with a sound recorder while implementing curriculum activities: in total, two sessions per activity (kindness curriculum, yoga-based activities, and emotion circle time) are registered and transferred to the principal investigators [TV, OC] to evaluate implementation fidelity. Fidelity is assessed for each record by two independent evaluators following a 3-question list inspired by Humphrey et al. [44]: (1) *Objectives: To what extent does the teacher cover the general and specific objectives of the lesson?* (2) *Structure: To what extent does the teacher follow the structure and sequence of activities outlined in the instruction manual?*; (3) *Content: How closely does the teacher adhere to the guidance manual when teaching the core activities of the lesson?*. Evaluators rate each question on a qualitative scale from 1 (= “Insufficient”) to 5 (= “Very satisfactory”). For each activity, scores for each question in each record for each evaluator are averaged into a total fidelity score on a 1-to-5 scale.

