## Assignment of interventions: allocation

### Sequence generation {16a}

Randomization was performed after having recruited 64 classes. Allocation sequence was generated online on the website randomizer.org by one of the principal investigators [TV] who will not be in charge of data collection, assessment, and analysis. Investigators in charge [OC, QD] are blinded to group allocation.

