## Assignment of interventions: blinding

### Who will be blinded {17a}

Investigators in charge of data analysis [OC, QD] are blinded regarding group allocations. Due to the nature of the experiment, teachers cannot be blinded regarding group status, as they deliver the program themselves. Evaluators assessing children in classrooms based on the *InClass* observation system and on experimental tasks are blinded both regarding group allocations and regarding the nature of the ongoing study. Blindness of evaluators regarding allocations and study nature is assessed at the end of the school year. Teachers in the classrooms are asked both orally and by written instructions not to communicate with evaluators regarding the study or the program, and had to answer to an email stating that they had received and understood these instructions.

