## Data collection and management

### Plans for assessment and collection of outcomes {18a}

Computerized teacher rating questionnaires (PKBS-Social Skills, STRS, SDQ) and questionnaires evaluating teacher characteristics (CHIME, WEMWBS, ESVP, Commitment measure) are collected in electronic form by a principal investigator blind to group allocation [OC]. Data encoding is verified by OC to detect software errors when encoding form data into a spreadsheet.

Tasks and observations are administered by trained evaluators, students in their third or fourth year of psychological or education sciences studies, who receive an intensive 3-day training and pass a certification test prior to school visits. During the first day of training, evaluators work by pairs through role-playing and learn how to administer each task, based on a manual with explicit instructions. They are also given advice for task processing and handling children. Ability to carry on reliably two randomly chosen tasks is evaluated by the principal investigators 3 days later. On the second and third day, evaluators are trained by certified trainers [OC, TV, VK] to use the InCLASS observation tool, using the standardized InCLASS training course. During this course, each InCLASS dimension is described to trainees with video examples, and they watch, code, and discuss five training video clips. To validate InCLASS training, evaluators are required to code five reliability clips independently and to obtain a correct response proportion of a least 80% for all InCLASS dimensions (and at least 3 correct responses for each dimension). Evaluators who are not reliable after this first test are given a second chance as they are asked to code five extra reliability clips. Evaluators who are still not reliable after this second step are excluded. Inter-rater reliability during the study is measured by collecting double-coding for one child during each visit, resulting in 12.5% double-coded InCLASS observations.

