### Methods for additional analyses (e.g., subgroup analyses) {20b}

We will estimate the effects of the intervention on the children’s and teachers’ outcomes listed in the “Outcomes {12}” section based on the following characteristics:Girls (for the children)Level of experience of the teachers (according to the median)Age of the teachers (according to the median)Initial levels of EF, connection, and problem behaviors of the childrenMulti-level classesTeachers predicted to have a high degree of commitment with the intervention by a machine learning model

According to the data collection plan detailed in this paper, we will ask questions about treatment-group teachers’ commitment with the intervention (see Plans for assessment and collection of outcomes {18a} section) and will average teachers’ answers into a standardized score of their commitment with the intervention. Then, we will run a Lasso regression [7] of that score on all the socio-demographic variables and the outcomes listed in the “Outcomes {12}” section measured at baseline, on the square of those variables, and on the products of all the pairs of variables. We will then use the Lasso regression to predict the commitment score of every teacher included in the experiment, hence including teachers in the control group. Finally, teachers predicted to have a high degree of commitment with the intervention will be those with a predicted score above the median. To compute predicted commitment with the intervention for treatment group teachers, we will use a leave-one-out method, as suggested by Abadie et al. [1]. It may however be the case that we are not able to predict the teachers’ commitment score very well, in which case, undertaking that third subgroup analysis would not be informative. If the Lasso regression does not select any variable, or if the R2 of the OLS regression of the commitment score on all the variables selected by the Lasso regression is below 0.1, we will not conduct that subgroup analysis.

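### The principal investigator who collects the questionnaires and leads the analysis is declared blind, yet is sent material that exists only for intervention teachers

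*Protocol article*

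**What the plan says.** Three sections of the protocol article declare the same investigator blind:

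- {16a}: "Investigators in charge [OC, QD] are blinded to group allocation".
- {17a}: "Investigators in charge of data analysis [OC, QD] are blinded regarding group allocations".
- {18a}: the computerised teacher forms "are collected in electronic form by a principal investigator blind to group allocation". The initials given there match the first set in {16a} and {17a}.

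Section {5d} says that this investigator carries out the data analysis, helped by the expert statistician.

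Other sections describe what reaches this person. Under {11c}, teachers record themselves in the middle of the school year while delivering the curriculum, with two sessions for each of the three activities. These recordings "are registered and transferred to the principal investigators", and both principal investigators are named there, including the one declared blind.

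The forms that this investigator collects under {18a} include "questionnaires evaluating teacher characteristics (CHIME, WEMWBS, ESVP, Commitment measure". The description of the commitment measure says "Teachers in the intervention group are asked about their commitment to implement the program using a single item". Section {20b} confirms this: "we will ask questions about treatment-group teachers’ commitment with the intervention", while control teachers receive only a predicted score.

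**The concern.** A person cannot stay blind to allocation while receiving material that only one arm produces. Control teachers are told to teach as in any other year, so a recording of a curriculum session can come only from an intervention class. A completed commitment form, which also asks whether the teacher liked the training, is just as revealing.

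What is at stake is mainly the analysis. Section {20a} lets covariates be added where they are judged to be needed, and groups outcomes into families that it does not list. There are 15 primary variables. A blind analyst is the stated protection against such choices being influenced, even without intent, by knowledge of the arms. If the results paper repeats the blinding statement, readers will credit the trial with a protection that its own data flow removes.

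**Working it through.** The protocol gives no figure to reproduce. The check sets the blinding statements beside the data flows and then counts.

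**Inputs**

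- Classes: 64, with 32 per arm ({8}).
- Activities recorded: 3, with 2 sessions each ({11c}).
- Timing: recordings in the middle of the 2021–22 school year ({11c}); T1 in May–June 2022 and T3 in May–June 2023 ({13}, {18a}).
- Access to the identity-code key: both principal investigators ({27}).
- Primary variables, by component in {12}: 4 + 2 + 2 + 3 + 4 = 15.

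**Side by side**

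| Declared | Described |
|---|---|
| Blind to allocation ({16a}, {17a}) | Named recipient of recordings from intervention classes ({11c}) |
| Collects teacher forms while blind ({18a}) | Those forms include one put to intervention teachers only ({18a}, {20b}) |
| Analyst is blind ({17a}) | The analyst is this same person ({5d}), who also holds the identity key ({27}) |

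**Count of recordings**

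- Per intervention teacher: 3 × 2 = 6.
- Maximum in total: 6 × 32 = 192.
- From control classes: 0.

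**What the recordings reveal**

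If all 32 intervention teachers comply, the list of senders identifies 32 intervention classes, and the other 64 − 32 = 32 must be control.

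If only k teachers send recordings, k classes are known with certainty, and the remaining 64 − k contain 32 − k intervention classes. As an illustration under an assumed half compliance, k = 16: 16 classes are known, and the other 48 hold 16 intervention and 32 control classes.

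Partial compliance does not rescue a coded-arm analysis by this person. All classes in one arm carry the same code, so linking one known intervention class to its code shows which code is the intervention.

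**Timing**

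Mid-year comes before May–June 2022, so the recordings are due before T1. The visible text does not date the commitment form, and the timeline table is not shown. Its item on whether pupils liked the content suggests a later date. The claim that blinding is lost before T1 therefore rests on the recordings alone.

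**The case against.** A reader might infer that blinding of data collection and analysis as a whole has failed. The documents do not support that. No section sends recordings or commitment forms to the statistician or to the evaluators who carry out the InCLASS observations and tasks. Under {17a} the evaluators are also blind to the nature of the study, teachers confirm in writing that they will not discuss it with them, and evaluator blindness is assessed at the end of the school year.

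A reader might also infer that allocation leaks to the evaluators, because this investigator helps to train them. That is speculation. {5d} has evaluators in contact with a principal investigator during visits without saying which one, and the investigator who generated the allocation is also one of their trainers.

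The effect on the questionnaire data is probably small. Teachers, who know their arm, complete the forms, and this investigator's stated task is to check for software errors in encoding. Section {20a} also fixes much of the analysis: regression on assignment, clustering at the unit of randomisation, weighted family indices and adjusted p-values. The trial status section bars analysis before the protocol is published.

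These points limit the harm, but they do not remove the contradiction. Independent evaluators rate fidelity under {11c}, yet the recordings still pass to the investigator declared blind, and no section describes a barrier. Condensation in a journal article does not explain it either, because both incompatible statements are printed.

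**Conclusion.** The protocol contradicts itself on the blinding of one principal investigator, who collects the questionnaires and is the main analyst. As the data flow is written, this person cannot be blind for the T1 and T3 analyses. The material concerned is at most 192 recordings, all from one arm, plus up to 32 commitment forms of unknown date. Identifying all 64 allocations from the recordings assumes full compliance; identifying some does not.

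The conclusion rests on reading the initials in {11c}, {16a}, {17a}, {18a} and {5d} as one person, and on the transfer taking place as described. It does not extend to the statistician or to the classroom evaluators, and it does not show that any result is biased. The consequence is that a stated safeguard on open analysis choices is missing for the person who makes them.

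**What to change.** In {11c} and {18a}, send recordings and commitment forms only to the investigator who generated the allocation. That person already knows the arms and, according to the Discussion, already monitors implementation with the teachers, so no new allocation knowledge is created. A research assistant would be a poor recipient, because {5d} has one corresponding with evaluators.

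Release fidelity and commitment data to the analysts only after the main T1 intention-to-treat models have been run on coded arms. The treatment-on-the-treated and Lasso analyses need those data and would follow.

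First-year recordings were due before T1 and may already have been received. In that case, state in {17a} that this investigator is not blind, and have the statistician run the main T1 and T3 models on coded arms, without access to the identity key or to the recordings. This assumes that the statistician is still blind, which should be confirmed.

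The cost is a change of recipient and file access, a short delay to the two secondary analyses, more analysis work for the statistician, and a less favourable blinding statement. No new staff or data are needed.
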